## Covid-19 addendum 200223

The Covid-19 pandemic puts a tremendous strain on the entire healthcare system, meaning that the STHLM3-MRI phase II study will be impacted and lead times for patients in the trial will become potentially very long. It is not unlikely likely (at the time of writing 200223) that the study will be prolonged by many months and even years. Therefore, we have decided to open up for the possibility to report on endpoints as they mature. I.e., if STHLM3MRI is unable to continue recruit participants and perform tests according to the study protocol, we open for the possibility to not have one finalized database lock that will be used for all analyses. Rather, we may then lock a database for a specific analysis when there is enough data in the study to test the hypothesis corresponding to the analysis. In particular, we already have enough data collected in the trial for Publication 1. From an ethical point of view, we believe this is the least bad possible approach under the current circumstances. We have a large dataset already collected in the study and we believe that it makes sense to use these data to benefit of patients as soon as possible for the endpoints and analyses that are possible to analyse, rather than waiting for a limited set of men who are left in the study and -- due to Covid-19 -- may not be able to complete the study protocol for a very long time. This plan has been communicated to and approved by the trial's DSMB.

Additional comment written 200905: The trial could be completed despite the covid-19 pandemic, and the addendum above will not have to be activated. This means that we will have one single database lock for performing all analyses, as originally planned.

## Post-hoc analyses

Ignoring biopsy results on men with negative MRI and Stockholm3  $\geq 25\%$

In order to estimate results in the counterfactual scenario where participants with negative MRI and Stockholm3  $\geq 25\%$  would not have been referred to undergo systematic biopsy, we will perform analyses where these biopsies are ignored. To be clear, we will not exclude these men from the analyses, but ignore their biopsy and biopsy outcome (i.e., they would enter the analyses as not having had a biopsy or any potential cancer diagnosis). The participants with a negative MRI and Stockholm3  $\geq 25\%$  will in these analyses thus contribute to the counts of performed MRI scans, but not to the count of biopsies or the cancer count. Apart from this, the analyses will be performed identically as detailed above.

## Appendix 1

Let  $T$  and  $S$  be the events “SBx+TBx positive for a specific ISUP grade” (eg, ISUP $\geq 2$ ) and “SBx positive for a specific ISUP grade”, respectively. Let  $P$  be the event “PSA screening test above 3 ng/ml”. Let  $D$  be the event “the subject is positive for a specific ISUP grade (true, unobservable status)”.

The main between-arm contrast of Study 1, expressed in relative terms, is given by

$$\frac{\Pr(T = 1|P = 1)}{\Pr(S = 1|P = 1)}.$$

This can be rewritten as:

$$\begin{aligned} \frac{\Pr(T = 1|P = 1)}{\Pr(S = 1|P = 1)} &= \frac{\Pr(T = 1, D = 1|P = 1) + \Pr(T = 1, D = 0|P = 1)}{\Pr(S = 1, D = 1|P = 1) + \Pr(S = 1, D = 0|P = 1)} \\ &= \frac{\Pr(T = 1, D = 1|P = 1) + \Pr(T = 1|D = 0, P = 1)\Pr(D = 0|P = 1)}{\Pr(S = 1, D = 1|P = 1) + \Pr(S = 1|D = 0, P = 1)\Pr(D = 0|P = 1)} \quad [\text{assumption}] \\ &= \frac{\Pr(T = 1|D = 1, P = 1)\Pr(D = 1|P = 1)}{\Pr(S = 1|D = 1, P = 1)\Pr(D = 1|P = 1)} = \frac{\Pr(T = 1|D = 1, P = 1)}{\Pr(S = 1|D = 1, P = 1)} = r_{TPF} \end{aligned}$$

The third equality holds under the assumption that the FPFs  $\Pr(T = 1|D = 0, P = 1)$  and  $\Pr(S = 1|D = 0, P = 1)$  are equal to zero, while the fourth equality hinges on the fact that — because of randomisation — the probabilities  $\Pr(D = 1|P = 1)$  in the two study arms are the same in expectation.

The equation above can be extended to the other between-arm contrasts.

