#### ***Definition of EXPERIMENTAL ARM***

Men randomized to the experimental arm undergoes MRI. If suspicious lesions are found, the participant undergoes targeted biopsies using Fusion technology *followed by systematic biopsies*.

Men without lesions are excepted from further intervention and receives notification on recommendation for follow-up. Technology and process are described below.

Men with a Stockholm3 risk  $\geq 25\%$  and no suspicious lesion on MRI will undergo systematic biopsies.

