### Revisions

| Date   | Authors  | Reason                              | Main changes                                                                                                                                                                        |
|--------|----------|-------------------------------------|-------------------------------------------------------------------------------------------------------------------------------------------------------------------------------------|
| 180217 | ME       | First draft of SAP                  |                                                                                                                                                                                     |
| 180515 | ME       | Feedback after initial DSMB meeting | Hypotheses and aims clarified.                                                                                                                                                      |
| 191115 | AD       | Updated sample size calculations.   | Updated sample size calculations to support decision to expand study in order to have sufficient power for within-arm comparisons of Stockholm3 vs. PSA in the experimental arm.    |
| 191127 | ME/AD/TN | Publication plan                    | Adjustment definition TBx. Introducing publication plan with 2 main manuscripts. Clarification and specification of the wording of the hypotheses. Clarification of follow-up time. |
| 200324 | ME       | Covid-19                            | Allow for potential analysis of the trial in two phases due to the Covid19 pandemic.                                                                                                |

|        |    |                                  |                                                                                                                          |
|--------|----|----------------------------------|--------------------------------------------------------------------------------------------------------------------------|
| 201223 | ME | Description of post-hoc analyses | Description of analyses where biopsies and biopsy results on men with negative MRI but Stockholm $\geq$ 25% are ignored. |
|--------|----|----------------------------------|--------------------------------------------------------------------------------------------------------------------------|

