## 9. (PSA | S3M)+MRI+TBx+SBx,

where (PSA | S3M) denotes positive on either PSA or S3M screening tests, SBx denotes systematic biopsies, and TBx denotes targeted biopsy. To be clear, only MRI positive men (PIRADS  $\geq 3$ ) are biopsied in the strategies that include MRI (apart from men with S3M  $\geq 25\%$ ). This is true irrespective of the biopsy procedure (i.e. SBx is also only performed in MRI positive men in these strategies) (Figure 1). ***The above strategies will in the rest of this document be referred to as Strategy 1, 2, 3, 4, 5, 6, 7, 8, and 9, respectively.***

Randomization stratified on disease risk [sextiles of the Stockholm3 test] will be used. Further, block allocation will be performed, with each block consisting of five men, two of which will be randomized to systematic biopsies and three will be randomized to the MRI arm. This means that randomization guarantees a proportional number of men in each arm and with more evenly distributed characteristics in terms of disease risk and test concordance.

[figure not shown]

**Figure 1:** Overview of the STHLM3 MR Phase 2 study design. Men aged 50-74 are invited to the study from the general population. Blood is sampled from study participants and PSA as well as Stockholm3 are measured. Men with elevated prostate cancer risk (PSA  $\geq 3$  ng/ml or Stockholm3  $\geq 11\%$ ) are randomized to be referred to either systematic biopsies (control arm) or undergo MRI and targeted plus systematic biopsies in case the MRI indicates areas of the prostate suggestive of prostate cancer (PIRADS  $\geq 3$ ). The design thus combines a paired step where PSA and Stockholm3 can be compared (paired screen positive design) and a randomized step where systematic biopsies can be contrasted to MRI and subsequent targeted and systematic biopsies for MRI positive men.

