## Publications strategy of main study results

A large number of publications will likely be written based on the data collected within the STHLM3MRI trial. The main study results from the trial will be reported in the two first publications:

## Publication 1

Publication 1 will as primary contrast report the comparison of Strategy 3 vs. 1 (PSA+MRI+TBx+SBx vs PSA+SBx). Additional analysis in the report will include contrasts of Strategies 2 vs 1.

This comparison uses only the randomized step of the trial design and is motivated by the need to provide level 1 evidence about the performance of MRI+targeted+systematic biopsies versus systematic biopsies alone in men with PSA  $\geq 3$  ng/ml in a screening-by-invitation context, where such data is lacking entirely. The choice of using systematic biopsies without MRI as the comparator hinges on the fact that, presently, this is the typical diagnostic strategy offered to men with an elevated PSA (Ahmed et al.). Furthermore, level 1 evidence about a mortality benefit from early detection of prostate cancer is available only for a diagnostic strategy based on PSA+systematic biopsies (Schröder et al. 2009 and 2014). Thus, Publication 1 will assess whether introducing PSA+MRI+TBx+SB into prostate cancer screening can diagnose clinically significant prostate cancer with non-inferior sensitivity to PSA+SB, for which there is level 1 evidence of a reduction in prostate cancer mortality. Publication 1 will cover additional hypotheses 1 and 2.

## Publication 2

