### Study populations

1. *ITT population* includes all men who:
  - a. signed the written informed consent to participate in the study,
  - b. fulfilled all inclusion criteria and none of the exclusion criteria,
  - c. were randomised to either study arm.

Conditions for excluding patients from the ITT population, based on deviations from the study protocol:

| Randomisation arm | MRI           | No biopsy | SBx only | TBx only | SBx and TBx |
|-------------------|---------------|-----------|----------|----------|-------------|
| Standard arm      | MRI or no MRI | Include   | Include  | Include  | Include     |
| Experimental arm  | MRI or no MRI | Include   | Include  | Include  | Include     |

Randomised allocation and analysis group for ITT analyses:

| Randomisation arm | Test received                           | Analysis group   |
|-------------------|-----------------------------------------|------------------|
| Standard arm      | Systematic biopsy (with or without MRI) | Standard arm     |
| Standard arm      | Targeted biopsy                         | Standard arm     |
| Standard arm      | Systematic biopsy and Targeted biopsy   | Standard arm     |
| Standard arm      | No biopsy / Other                       | Standard arm     |
| Experimental arm  | Systematic biopsy (with or without MRI) | Experimental arm |
| Experimental arm  | Targeted biopsy                         | Experimental arm |

|                  |                                       |                  |
|------------------|---------------------------------------|------------------|
| Experimental arm | Systematic biopsy and Targeted biopsy | Experimental arm |
| Experimental arm | No biopsy / Other                     | Experimental arm |

2. *PP population* includes men who:

- a. are included in the ITT population,
- b. have a valid PSA value and Stockholm3 score,
- c. have a complete systematic pathology report if randomised to standard arm (but no targeted pathology report),
- d. have a complete MRI report if randomised to experimental arm and (i), (ii), or (iii), as appropriate,
  - i. have a complete systematic and a complete targeted pathology report if PIRADS $\geq$ 3,
  - ii. have a complete systematic pathology report if PIRADS $<$ 3 and Stockholm3 $\geq$ 25% (but no targeted pathology report),
  - iii. did not undergo any biopsy if PIRADS $<$ 3 and Stockholm3 $<$ 25%.

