#### *Contrasts between study arms (unpaired design)*

Analyses will compare the difference in detection probabilities (DPs) between study arms. The DP is the probability of being endpoint-positive given the study arm and, possibly, either or both screening tests being positive. For example the DP of ISUP1 in men randomised to the experimental arm and Stockholm3-positive is equal to  $\Pr(\text{ISUP1} \mid \text{Stockholm3} \geq 11\%, \text{Experimental arm})$ .

**Absolute scale.** The absolute difference in DPs is defined as the DP in the experimental arm minus the DP in the standard arm ( $\Delta\text{DP} = \text{DP}_{\text{Exp}} - \text{DP}_{\text{Std}}$ ) or vice versa, as appropriate. It is estimated by plugging into the formula the observed proportions. An approximate 100(1- $\alpha$ )% two-sided Wald confidence interval for  $\Delta\text{DP}$  is calculated as

$$\widehat{\Delta\text{DP}} \pm z_{\alpha/2} \sqrt{\frac{\widehat{\text{DP}}_{\text{Exp}}(1-\widehat{\text{DP}}_{\text{Exp}})}{n_{\text{Exp}}} + \frac{\widehat{\text{DP}}_{\text{Std}}(1-\widehat{\text{DP}}_{\text{Std}})}{n_{\text{Std}}}}.$$

**Relative scale.** The relative difference in DPs is defined as the DP in the experimental arm divided by the DP in the standard arm ( $r\text{DP} = \text{DP}_{\text{Exp}}/\text{DP}_{\text{Std}}$ ) or vice versa, as appropriate. It is estimated by plugging into the formula the observed proportions. An approximate 100(1- $\alpha$ )% two-sided Wald confidence interval for  $r\text{DP}$  is calculated as

$$\exp\left(\log(\widehat{r\text{DP}}) \pm z_{\alpha/2} \sqrt{\frac{1}{\widehat{\text{DP}}_{\text{Exp}} * n_{\text{Exp}}} - \frac{1}{n_{\text{Exp}}} + \frac{1}{\widehat{\text{DP}}_{\text{Std}} * n_{\text{Std}}} - \frac{1}{n_{\text{Std}}}}\right).$$

Contrasts 3 vs 1, 2 vs 1, and 9 vs 7 will be analysed using absolute differences (Study 1). Contrasts 6 vs 1, and 5 vs 1 will be analysed using relative differences (Study 2).

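### In Publication 1's primary contrast (3 vs 1), the PSA+MRI strategy is credited with cancers found only because Stockholm3 was 25% or higher, which favours non-inferiority for the pathway as named

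*Combined protocol and SAP*

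**What the plan says.** **The biopsy rule.** Protocol section 13.4 (definition of the experimental arm) states that men with Stockholm3 of 25% or more "and no suspicious lesion on MRI will undergo systematic biopsies". The SAP's Design section gives safety as the reason.

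**How strategies are defined.** After listing the nine strategies, the SAP Design section says that only MRI-positive men "are biopsied in the strategies that include MRI (apart from men with S3M" of 25% or more). The exception is not restricted to the Stockholm3-based strategies, so it also covers Strategy 3 (PSA+MRI+TBx+SBx).

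**Who is analysed.** Under Study populations, the ITT set keeps every randomised man whatever biopsies he had. The PP set keeps MRI-negative men with Stockholm3 of 25% or more if they have a complete systematic report. Neither rule depends on which screening test is being assessed.

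**The contrast.** "Publication 1 will as primary contrast report the comparison of Strategy 3 vs. 1". It is presented as a test of bringing PSA+MRI+TBx+SBx into screening. It is analysed on the absolute scale: "Contrasts 3 vs 1, 2 vs 1, and 9 vs 7 will be analysed using absolute differences (Study 1").

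**The analysis without these biopsies.** It is described under Post-hoc analyses, with the subheading "Ignoring biopsy results on men with negative MRI and Stockholm3" of 25% or more. The men stay in as not biopsied and without cancer, and everything else is unchanged. The Revisions table enters it at 201223: "Description of analyses where biopsies and biopsy results on men with negative MRI but Stockholm" of 25% or more are ignored. No pre-specified main or sensitivity analysis does this.

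**The concern.** A screening programme that selects men on PSA and then uses MRI has no Stockholm3 score. It could not order a biopsy because that score is 25% or more. Strategy 3, as analysed, nevertheless receives both the biopsies and the cancers they find.

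Two features make this matter for non-inferiority. The added procedure is systematic biopsy, which is the control procedure. It is given to high-risk men with a negative MRI, the group in which an MRI-triggered pathway can miss cancer. Both features move the experimental arm towards the control arm, which is the unsafe direction when the aim is to show non-inferiority.

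At stake is whether a 3 vs 1 result inside the 4-point margin can be read as evidence about PSA+MRI, or only about PSA+MRI with a Stockholm3 safety net. The number of biopsies charged to Strategy 3 is also too high for the named pathway.

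**Working it through.** **Inputs from the documents**
- Control detection of ISUP ≥2 in men with PSA ≥3 on systematic biopsy: 18% (SAP, original sample size).
- Margin 4 points; one-sided alpha 0.025.
- Planning ratio rDP = 1.3, so experimental detection is 0.18 × 1.3 = 23.4% (SAP, updated sample size).
- About 1600 randomised men with PSA ≥3, allocated 2:3, giving 640/960. After 20% dropout, 1280 men, giving 512/768.
- 55% MRI-negative overall (protocol addendum).

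**Inputs the documents do not give (assumed)**
- Share of PSA ≥3 men with Stockholm3 ≥25%: 20%.
- MRI-negative among them: 30% to 55%. The upper value is the overall rate.
- ISUP ≥2 yield of systematic biopsy in those men: 10% to 20%.

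**Step 1. Reproduce the stated power for 3 vs 1.** With the SAP's Wald variance,

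SE = √[pC(1−pC)/nC + pE(1−pE)/nE], power = Φ[(pE − pC + 0.04)/SE − 1.96].

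For pC = 0.18, pE = 0.234 and 512/768 men, SE = 0.0228 and power = Φ(0.094/0.0228 − 1.96) = 98.4%. With 640/960 it is 99.6%. Both agree with the SAP's statement of more than 90%.

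**Step 2. Size of the credit, c.** c = share × P(MRI-negative) × yield.
- Low: 0.20 × 0.30 × 0.10 = 0.6 points.
- High: 0.20 × 0.55 × 0.20 = 2.2 points.

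Among 768 men this is about 5 to 17 cancers (0.006 × 768 = 4.6; 0.022 × 768 = 16.9). The added biopsies are 0.20 × 0.30 = 6 to 0.20 × 0.55 = 11 per 100 PSA-positive men.

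**Step 3. Error rate when the true PSA+MRI pathway sits at the margin.** Set its detection at 14%, so the analysed rate is pE = 0.14 + c.

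| c (points) | 640/960 | 512/768 |
|---|---|---|
| 0 | 2.5% | 2.5% |
| 0.6 | 5.0% | 4.7% |
| 1.0 | 7.6% | 6.8% |
| 2.2 | 20.6% | 17.4% |

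The 512/768 column is the closer match, because 18% is a rate in biopsied men.

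**Step 4. Power if the credit is removed.** At the planning value, pE = 0.234 − c with 512/768 men. Power is 97.2% (c = 0.6), 95.9% (c = 1.0) and 89.3% (c = 2.2). It stays above 90% until c is about 2.1 points.

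**Step 5. Direction in 6 vs 3.** The SAP estimates the Stockholm3/PSA ratio as (a'+b')/(a'+c'). A cancer in a PSA-positive, MRI-negative man with Stockholm3 ≥25% is counted in a'. Moving k such cancers to b' leaves the numerator unchanged and cuts the denominator by k. With a'+c' = 100 and k = 5 (illustrative), 0.90 becomes 90/95 = 0.95, 1.00 becomes 100/95 = 1.05, and 1.20 becomes 120/95 = 1.26. The as-performed ratio is therefore always the lower one.

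**The case against.** **The exception is disclosed and the comparison is randomised.** This stands. For the pathway delivered in the experimental arm, 3 vs 1 is unbiased. A reader might infer that the randomised comparison itself is invalid; the documents do not support that. The mismatch is between the delivered pathway and the one named and interpreted in Publication 1.

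**The trial's primary hypothesis is 6 vs 1.** This also stands. Strategy 6 has the Stockholm3 result, so the exception belongs there and that contrast is untouched.

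**The SAP already describes the needed analysis.** For 3 vs 1 it does, and exactly. Only its status is in dispute. A reader might take the post-hoc label to mean it was added after results were seen. The SAP dates the entry but does not say whether it preceded database lock.

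**The size is assumed.** Correct. The direction follows from the definitions, but the share and yield do not. At the planning value, non-inferiority would usually be shown with or without these biopsies.

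**Other tempting extensions.**
- One might say that 6 vs 3 is pulled towards 1. Step 5 shows that it is lowered whatever its value, which is conservative for Stockholm3 non-inferiority against 0.78. The SAP presents this contrast as a comparison of tests for selecting men for workup, so giving both sides the same workup is defensible.
- One might say that Strategy 2 is affected equally. It uses targeted biopsies only, and the SAP does not say whether a systematic-only result counts in it.
- One might recode every man with PI-RADS below 3 as not biopsied. That would also erase off-protocol biopsies which the ITT rules keep, in one arm only.

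The effect also does not favour the experimental arm on every endpoint. For ISUP 1 and biopsies performed, the same biopsies count against it.

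**Conclusion.** The point holds for 3 vs 1, as a mismatch between what is estimated and what the strategy is called. Counting these cancers can only raise Strategy 3's ISUP ≥2 rate, so it favours non-inferiority for PSA+MRI+TBx+SBx; it also raises the biopsy count. Confidence in the direction is high. The size depends on a share and a yield that the documents do not report. Under the assumed credit of 0.6 to 2.2 points, the one-sided error at the margin is about 5–21% with 640/960 men, or about 5–17% with 512/768, instead of 2.5%.

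Strategy 2 is an open definition, not an established error. In 6 vs 3 the planned analysis is conservative for Stockholm3 non-inferiority and does not need replacing. This should be changed, but it does not invalidate the trial.

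**What to change.** 1. For 3 vs 1, make the analysis now under Post-hoc analyses the main one. Men with both a negative MRI and Stockholm3 of 25% or more stay in the denominator as not biopsied and without cancer. All other men are analysed under the existing ITT and PP rules. Report the as-performed result as a sensitivity analysis.
2. State in the SAP whether systematic-only results in these men count in Strategy 2. If they do, treat 2 vs 1 in the same way.
3. For 6 vs 3, keep the as-performed analysis. At most, add a sensitivity analysis that moves these cancers from a' to b', noting that this makes Stockholm3 non-inferiority easier to show.
4. Report the number of these men with PSA ≥3 and their ISUP ≥2 yield, so that the credit is known and not assumed.

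The cost is a change of SAP wording and a reclassification of data already collected. The Strategy 3 detection rate becomes slightly less favourable, and power for 3 vs 1 at the planning value falls from 98.4% to about 97% to 89% over the assumed range with 512/768 men. Patient care does not change.
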